#### Hypotheses

We hypothesize that an integrated personalized assistive devices approach in addition to usual care will significantly lower the proportion of people with foot ulcer recurrence, significantly increase adherence to wearing custom-made footwear, and save costs per quality-adjusted life year gained, compared to usual care alone in people with diabetes at high risk of foot ulceration. These hypotheses are based on the superiority of the intervention compared to usual care, studied in a multicenter RCT.

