### Outcomes {12}

There are three primary study outcomes in this study, which are:Foot ulcer recurrence during the 12-month follow-upAdherence to wearing custom-made footwearThe cost (savings) per quality-adjusted life year (QALY) gained (i.e., cost-utility)

These represent a clinical, patient-related, and health-economic perspective, respectively. Foot ulcer recurrence is defined as “a break of the skin of the foot that involves as a minimum the epidermis and part of the dermis, in a person who has a history of foot ulceration, irrespective of location and time since the previous foot ulcer” [15], is monitored during the entire study period, and is—on group level—calculated as the proportion of participants with one or more foot ulcers during the study period. Footwear adherence is defined as the percentage of steps taken in prescribed footwear, calculated by combining physical activity and wearing time measurements [44]. It is calculated over 1 week, at baseline and (for outcomes) at 6 and 12 months’ follow-up. Cost-utility is monitored during the entire study period, costs are summed throughout the 12-month period [45], and utility is scored with the EQ-5D-5L questionnaire every 3 months [46].

Secondary study outcomes are as follows: proportion of participants with one or more recurrent foot ulcers on the plantar side of the foot [15]; proportion of participants with one or more recurrent foot ulcers at the predefined personalized high-risk locations [15]; ulcer-free survival days [47]; falls [48]; wearing time of custom-made footwear [49]; in-shoe peak plantar pressure [47]; cumulative plantar tissue stress [44]; footwear wear-and-tear [50]; ulcer risk prediction score [29]; treatment and footwear satisfaction [51]; foot-related self-care [52]; knowledge of foot care [53]; capabilities, opportunities, and motivations (COM-b) score [54]; quality of life (in participants with [55, 56] or without [5] a recurrent foot ulcer during the trial); physical activity [57]; costs [45]; QALYs [46]; and cost-effectiveness [45]. In participants with an ulcer, other secondary outcomes are as follows: time to ulceration [58], ulcer severity [59–61], time to healing [58], and referral time [62]. Definitions for all secondary outcomes are as provided in the reference following each secondary outcome. All secondary outcomes are monitored during the entire study period using assessments and questionnaires during follow-up visits (see Fig. 2).

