For cost-utility as primary health-economic outcome measure, we anticipate a clinically relevant 0.1 gain in QALYs for the enhanced therapy group with group standard deviations for QALYs of 0.15 [64]. We use an estimation of cost difference of €0 per participant between both groups with group standard deviations for costs of €1000 [65, 66]. We allow room here for a more positive outcome in costs, as we predict an average cost saving per participant of €1113.75 for enhanced therapy based on the expected clinical effect of 59% relative reduction in number of ulcers compared with usual care (see Table 1). With a willingness to pay (WTP) of €50,000, a correlation between costs and QALYs (*ρ*) of 0, *α* = 0.05 (two-sided), power = 80%, and a drop-out rate of 20%, this leads to a sample size of 63 participants per study group, or 126 participants in total. Without drop-out, a sample size of (63 × 0.8 =) 51 participants per study group or 102 in total is required.

**Table 1 Tab1:** Average predicted costs per participant

				**Enhanced therapy**		**Usual care**	
**Modality**	**Event/activity**	**Time (hours)**	**Unit costs**	**Expected frequency**	**Expected costs**	**Expected frequency**	**Expected costs**
	Ulcer development [6]	-	€10,000	0.15	€1500	0.37	€3700
	Podiatrist	1	€100	0.50	€50	0.00	€0
Custom-made footwear	Optimization equipment: pressure measurements [36]	-	€50	1.00	€50	0.00	€0
	Shoe technician	1	€100	2.00	€200	0.00	€0
Custom-made indoor footwear	Production and optimization [13]	-	€400	0.95	€380	0.00	€0
Personalized temperature monitoring	Thermometry [38]	-	€75	0.75	€56.25	0.00	€0
Personalized education	Structured education	1	€100	0.50	€50	0.00	€0
	Motivational Interviewing	1	€100	2.00	€200	0.00	€0
	Equipment [49, 57]	-	€100	1.00	€100	0.00	€0
**Total**					€2,586.25		€3,700

Average of predicted additional costs per participant of enhanced therapy versus usual care, based on the expected frequencies as described in the power calculation. For all costs except ulcer development, usual care is used as index. Unit cost estimations are based on previous studies and standard hourly wages of a college educated professional in the Netherlands

With the power calculations showing a requirement of 122 participants for the primary clinical outcome, 120 for the primary patient-related outcome, and 126 for the primary health-economic outcome, a sample size of 126 participants provides adequate power for all three primary outcomes.

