### Statistical methods

#### Statistical methods for primary and secondary outcomes {20a}

Statistical analysis will be performed after the last follow-up visit of the last participant using SPSS statistical software (IBM Corporation, Armonk, NY). All tests will assess group effects, will be two-sided, and use *P* < 0.05 as significance level. All comparisons between groups are based on both intention-to-treat and final visit end-point analysis.

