##### Other study outcomes

Differences in costs and QALYs between enhanced therapy and usual care will be assessed using independent samples *T*-tests, with 95% bias-corrected and accelerated confidence intervals around the mean difference to account for sampling variability, stratified for a maximum of two variables that are univariately associated with the outcome. For cost-effectiveness, the approach will be identical to the approach for cost-utility described above, with foot ulcer recurrence as the clinical outcome. For all other study parameters (see the “Outcomes {12}” section), differences between enhanced therapy and usual care will be assessed via independent sample* T*-tests (for normally distributed data) or Mann–Whitney *U*-tests (for not normally distributed data) in case of interval or ratio data, and with chi-square or Fisher’s exact tests in case of nominal or ordinal data.

In addition, a budget impact analysis (BIA) will be done. The budget impact analysis will be carried out from governmental, health care provider, and insurer perspectives. The governmental perspective is chosen to help setting priorities in health care optimization while simultaneously considering the wider implications of stimulating enhanced therapy for diabetic patients at a high risk of ulcers beyond the health care sector. The provider perspective is chosen to support local decisions on economies of scale and affordability. The insurer perspective is chosen to assess the net financial consequences of offering intensified monitoring to high-risk patients who already have had ulcers in the past, which may help to shift health care use from the second to the first echelon. The BIA will be conducted using a decision-tree model developed in Microsoft® Excel. The BIA will be performed according to the Professional Society for Health Economics and Outcomes Research Task Force principles. We will use multiple scenarios with different numbers for the population to target, different treatment adherence, and different implementation scenarios, based on the best estimates available at the time of analysis.

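### Ordinal secondary outcomes are assigned to chi-square or Fisher's exact tests, which ignore the order of the categories and lose power against a shift in one direction

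*Protocol article*

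**What the plan says.** The rule stands in the protocol article under Statistical methods {20a}, Other study outcomes. After costs, QALYs and cost-effectiveness are dealt with, one rule covers everything else: "For all other study parameters (see the “Outcomes {12}” section), differences between enhanced therapy and usual care will be assessed" by a test chosen according to measurement level. T-tests are for normally distributed data, and the alternative is "Mann–Whitney *U*-tests (for not normally distributed data) in case of interval or ratio data". Categorical data are handled "with chi-square or Fisher’s exact tests in case of nominal or ordinal data".

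The general paragraph of {20a} adds: "All tests will assess group effects, will be two-sided, and use *P* < 0.05 as significance level". No rank test, trend test or ordinal regression is named for ordinal data anywhere in the article.

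Outcomes {12} lists the outcomes to which the rule applies, for example "footwear wear-and-tear [50]; ulcer risk prediction score [29]; treatment and footwear satisfaction [51"], with definitions left to the cited references. It also lists ulcer severity among participants who ulcerate. The section on unscheduled assessments says that ulcers are classified with the University of Texas system and the WIfI score. The article does not say which outcomes are treated as ordinal or how many categories each has.

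**The concern.** Reordering the categories leaves a chi-square or Fisher's exact p-value unchanged. With k categories and two arms, chi-square spreads its sensitivity over k − 1 degrees of freedom and so over every possible pattern of difference. For an ordered scale the usual question is whether one arm sits higher than the other, and a rank test or a proportional-odds model puts its sensitivity into that single direction.

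The rule is also the wrong way round. It uses ranks for skewed interval data, where they are one option among several, and discards order for ordinal data, where ranks are the natural choice.

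Two things are at stake. A real improvement on an ordinal outcome is more likely to be missed. A significant result may also reflect a difference in spread, which does not show that either arm did better.

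This is not a detail left to an analysis plan, because the protocol itself names the data type and fixes the test for it.

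**Working it through.** **Inputs from the article.** Two-sided α = 0.05 ({20a}); 126 participants allocated 1:1, so 63 per arm (Sample size {14}, Trial design {8}); 20% drop-out as used for two of the three primary outcomes, so 63 × 0.8 ≈ 50 per arm; ulcer rates of 37% and 15% ({14}).

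**Assumed inputs, because the article gives none.** 3 to 7 categories; equal category frequencies under usual care in the table below (skewed and symmetric distributions gave similar results); a common cumulative odds ratio of 1 to 4. With 5 equal categories, for instance, an odds ratio of 2.5 turns 20% in each into about 9, 12, 16, 24 and 38%.

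**The plan's own figure first.** No power is stated for any ordinal outcome. The nearest figure is 61 per group for ulcer recurrence. With p̄ = 0.26, n = [1.960·√(2·0.26·0.74) + 0.842·√(0.37·0.63 + 0.15·0.85)]² / 0.22² = (1.216 + 0.505)² / 0.0484 ≈ 61.2. Rounded up this is 62 against the stated 61, and power at 61 is 79.9%. The figure is reproduced. That outcome is binary, so category order plays no part in it.

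**Analytic check.** Let the ordered 1-df test have 80% power. Its non-centrality is λ = (1.960 + 0.842)² ≈ 7.85. If the departure is a pure shift, chi-square has about the same λ on k − 1 df, and its power is P(χ²[k − 1, λ] > critical value):

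| Categories | df | 5% critical value | Chi-square power | Loss from 80% |
|---|---|---|---|---|
| 3 | 2 | 5.99 | 71% | 9 points |
| 4 | 3 | 7.81 | 64% | 16 points |
| 5 | 4 | 9.49 | 60% | 20 points |
| 7 | 6 | 12.59 | 52% | 28 points |

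**Simulation.** Pearson chi-square against tie-corrected Mann–Whitney, at least 20,000 replicates per scenario. At odds ratio 1 both tests reject about 5% of the time. Power in %, chi-square / Mann–Whitney, 63 per arm:

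| Categories | OR 1.5 | OR 2 | OR 2.5 | OR 4 |
|---|---|---|---|---|
| 3 | 18 / 23 | 45 / 55 | 68 / 78 | 96 / 98 |
| 4 | 16 / 25 | 41 / 58 | 65 / 81 | 95 / 99 |
| 5 | 15 / 25 | 37 / 58 | 61 / 82 | 94 / 99 |
| 7 | 12 / 25 | 31 / 59 | 54 / 83 | 92 / 99 |

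At OR 2.5 the losses are about 9, 15 to 16, 20 to 21 and 29 points; repeated runs differ by about a point. At 50 per arm and OR 2.5 the pairs are 58/68, 53/71, 50/72 and 42/73. The smallest loss is about 2 points (3 categories, OR 4, 63 per arm) and the largest about 30 (7 categories, OR 2.5, 50 per arm). A 10-category scale, outside the main range, reached 38.

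Fisher's exact test was not simulated. It shares the defect, since it too is unchanged when categories are reordered.

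**Ulcer severity.** At the planned rates about 0.37 × 63 ≈ 23 usual-care and 0.15 × 63 ≈ 9 enhanced-therapy participants have an ulcer to grade. At an assumed odds ratio of 3 with 3 to 5 categories, power is 15 to 25% for chi-square and about 30 to 33% for the rank test, a loss of 8 to 17 points.

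**Where chi-square does better.** With 5 categories and 63 per arm, take 10/20/40/20/10% against 20% in each, which changes spread but not location. Chi-square has about 63% power and Mann–Whitney about 5%.

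**The case against.** The strongest reply has four parts.

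- **The test is valid.** Type I error is held, no primary outcome is involved, and the power claim that "a sample size of 126 participants provides adequate power for all three primary outcomes" is untouched. All of this stands. A reader might infer that a main conclusion of the trial is at risk, and the article gives no ground for that.
- **No affected outcome is established.** Scales are left to cited references. COM-b is called a score and, if treated as interval data, already goes to a t-test or Mann–Whitney test. Satisfaction, wear-and-tear and knowledge items are only possible candidates. This stands as a limit on reach. Still, the authors wrote a rule for ordinal data, so they expect some. Ulcer severity is the clearest case, although about 32 ulcerated participants give low power with either test.
- **The size is not fixed by the document.** A reader might quote 15 to 28 points as a general loss. That range belongs to 4 to 7 categories when the rank test has about 80% power. With 3 categories, or with a weak or very strong shift, the loss is smaller.
- **Chi-square sees patterns that ranks miss.** This is true, as the spread example shows, so it would be wrong to say the power is given up for nothing. It is a trade-off, but a shift is the more usual interest on an ordered scale.

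It is also tempting to cite the Hypotheses section, "These hypotheses are based on the superiority of the intervention compared to usual care", as a stated direction for these outcomes. That section covers only ulcer recurrence, footwear adherence and cost-utility. The case against the rule therefore rests on the nature of ordered scales and not on a hypothesis written for these outcomes.

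**Conclusion.** The point holds as a poorly chosen test for ordinal secondary outcomes. Chi-square was weaker than the rank test in every one-directional shift examined, at the same 5% error. The loss of about 2 to 30 points is an illustration under assumed category counts (3 to 7), distributions and odds ratios (1.5 to 4), and should be quoted only with those conditions. The mechanism is certain; the magnitude for this trial and the number of outcomes affected are not known from the article. Binary outcomes are not affected, because with two categories there is no order to lose. The point is worth correcting, but it does not bear on the trial's primary conclusions.

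**What to change.** Replace the last part of the rule under Other study outcomes with wording such as: *Mann–Whitney U-tests (tie-corrected) for ordinal data and for non-normally distributed interval or ratio data; chi-square or Fisher's exact tests for nominal data.* Alternatively, analyse ordinal outcomes by proportional-odds regression and report a common odds ratio with its 95% confidence interval, which also gives an effect estimate. It would help to list which secondary outcomes count as ordinal.

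The cost is one sentence. Mann–Whitney is already in the plan, and no extra data, visits or participants are needed. The change should be recorded before the data are analysed, so that the test is not chosen after results are seen. The downside is lower sensitivity to differences in spread without a shift; showing the full category distribution by arm would keep such differences visible.

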#### Interim analyses {21b}

Not applicable. This trial will not have an interim analysis.

#### Methods for additional analyses (e.g., subgroup analyses) {20b}

Various per-protocol analyses will be done, consisting of (i) adherence to the modalities in enhanced therapy and (ii) adherence to each specific modality in enhanced therapy, comparing adherent participants with both non-adherent participants and with the control group, and (iii) for each modality that is part of the intervention, we will compare outcomes of all participants who received that modality (including those in usual care, since the separate parts of the intervention can be provided in usual care) with participants who did not receive that modality.

Subgroup analyses will be done based on gender, ethnicity, disease severity (e.g., ulcer history, comorbidities), education level, and disease perceptions (e.g., perceived ulcer risk), to assess their associations with all outcomes.

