#### Self-care and self-management

Another cornerstone of ulcer prevention is regular foot inspection, self-care, and self-management. Current guidelines recommend patients to check and monitor their feet and footwear on a daily basis [7]. If patients are adherent, fewer ulcers recur [15]. To enhance regular foot inspection, daily monitoring of contralateral differences in foot temperature is a self-management strategy recommended in current guidelines [7], based on the outcomes of multiple randomized controlled trials (RCTs) [16–20]. Temperature differences are not seen or felt because of sensory neuropathy, but can easily be measured and monitored by patients themselves using a thermometer. A local increase in foot temperature, i.e., a “hotspot,” can be a preliminary sign of inflammation preceding ulceration [16–18, 20]. A meta-analysis of RCTs shows that daily monitoring of foot temperature reduces the risk of foot ulcers by around 25% [21]. Key in this self-management strategy is that the signaling of a hotspot is followed by taking the pressure off the foot with decreasing ambulatory activity; adherence to this part of the strategy resulted in a significantly higher ulcer risk reduction [20]. However, adherence to daily monitoring of foot temperatures has shown to be low in almost 40% of study participants, and only around 25% of participants who measured a hotspot decreased their ambulatory activity [20]. Daily self-management for ulcer prevention is often seen as a burden, and daily thermometry adds to that burden [22], explaining some of the low adherence. And while daily foot temperature monitoring is a promising prevention method, to date the method is hardly implemented in clinical practice. Adjustments in the intervention seem to be needed to improve usability and adherence and decrease the patient burden, for example by personalizing the measurement locations [20]. The effects of these adjustments need to be investigated.

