### Interventions

#### Explanation for the choice of comparators {6b}

Participants will be randomly assigned to either enhanced therapy or usual care. The comparison to usual care was chosen as being the current standard of care in the Netherlands of which participants cannot be deprived for ethical reasons. Enhanced care includes the intervention under investigation in addition to usual care, as it is key to prove that enhanced therapy is superior to usual care. Usual care consists of care as provided to high-risk people with diabetes in the Netherlands, following national and international guidelines and standards [33–35]. This includes foot care and screening by a podiatrist, a contracted diabetes pedicure, and if needed, a multidisciplinary team, every 1–3 months [33]. It also includes custom-made footwear that may or may not already be evaluated using in-shoe plantar pressure assessment as usual care in some centers. Usual care may thus include one or more of the enhanced therapy interventions, although in usual care these interventions are mostly offered in a less structured way, not according to a state-of-the-art protocol, not as an integrated approach, and without much personalization to the approach.

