**Fig. 1 Fig1:**
[figure not shown]
Schedule of intervention modalities. All follow-up visits can deviate a maximum 2.5 weeks from the scheduled timepoint. RAND, randomization visit; FU_x_, follow-up visit (numbered by visit number); UV, unscheduled visit; FV, final visit

At the start of the inclusion, each participant possesses custom-made footwear, as defined in the inclusion criteria, that will be assessed on shoe and insole design features. In the enhanced therapy group, this footwear will be checked against the latest standards, as described in the state-of-the-art design protocol for custom-made footwear [9]. As part of this protocol, the footwear will be evaluated during walking using in-shoe plantar pressure analysis (Pedar-X system, Novel GmbH, Munich, Germany). Footwear will be targeted for pressure improvement if peak pressures are > 200 kPa or if the research team and shoe technician believe a more optimal pressure result is feasible. The aim is to reduce peak pressure with 25% compared to baseline or to an absolute level below 200 kPa. Every 3 months, the top layer of the insoles will be replaced, as previous research showed this to be a key pressure-reducing intervention, likely because of wear and tear of the top cover [36]. After 6 months, the custom-made footwear will be re-evaluated using in-shoe plantar pressure measurements and modified if needed, following the same protocol as described above if peak pressures are > 200 kPa or improvement is considered feasible by the team.

B. Custom-made indoor footwear

Alongside the regular custom-made footwear that participants already have, custom-made footwear specifically for indoor use will be designed and manufactured [13]. The manufacturing procedure will be explained to participants, and the potential benefits and harms will be discussed. While recommended to have the indoor footwear prescribed, participants are free to accept or decline the custom-made indoor footwear. If a participant declines custom-made indoor footwear, the option will again be discussed in 3 months. If a participant then decides to have custom-made indoor footwear prescribed, the above procedures will be followed.

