During the first 2 weeks, participants will measure foot temperatures daily and record findings in a logbook. This run-in period is used for participants to become acquainted to the measurements and for the researchers to receive indications of the participant’s fluctuations in foot temperature over a 2-week period. After this run-in period, participants will still measure temperatures daily, but the participant can choose whether or not temperatures are recorded in the logbook. When an above-threshold temperature difference is found, participants are instructed to record these instances in the logbook.

At each study visit, participant experiences with and adherence to the at-home foot temperature measurements will be discussed, as well as the added value based on the frequency that hotspots are found. If the participant reports the temperature measurements to be a burden and considers to discontinue measurements, alternative solutions to personalize the measurement protocol and lower the burden will be discussed and if needed implemented. The researchers may also decide it is no longer of value to continue the temperature measurements with a participant, for example when a hotspot is never measured. Both outcomes contribute to the personalization of treatments that is key in this study.

D.Personalized education

Throughout the intervention, participants will receive structured education during their study visits provided by the investigator. The education will be structured using the “Fragile Feet – Trivial Trauma” (FFTT) model [39]. The model will be personalized, to reflect the situation of the individual participant, based on the presence or absence of risk factors as obtained during baseline screening. The personalized FFTT model will be provided to the participant on a printed leaflet and will be used to guide the participant through an explanation of multiple risk factors and the intervention modalities that reduce these risks. A collaborative approach in discussing these interventions will be taken [40], in a first-person narrative [41]. Participants will be asked to explain the leaflet in their own words to check for their understanding, to allow for teach-back [42].

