A potential limitation in this trial is the multiplicity and diversity of treatments offered. Our main goal is to offer a combined treatment approach that is representative of a combination of treatments that patients can receive in usual care, but personalized and optimized in a structured fashion. While this is a strength from the perspective of generalizability, it may not be possible to determine the individual contribution of the modalities to the overall effect. Another limitation is that all interventions offered can currently be part of usual care, which, if the case, may mask an effect between enhanced therapy and usual care. Although it is known that these interventions are not widely implemented in Dutch healthcare for diabetic foot disease [27], this is a potential threat to group contrast. However, by conducting a per-protocol analysis for both the combined interventions and for each specific modality, we aim to gain further insights into the effects of the individual treatment modalities. This analysis will include participants of the control group who receive one of the enhanced therapy interventions as part of usual care.

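### The per-protocol and modality comparisons use groups formed after randomisation, and the pooled received-versus-not comparison credits the whole enhanced-therapy bundle to each single modality

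*Protocol article*

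**What the plan says.** The methods for additional analyses {20b} list three sets of per-protocol comparisons. Sets (i) and (ii) concern adherence to the modalities together and to each one, "comparing adherent participants with both non-adherent participants and with the control group". In set (iii), for each modality, "we will compare outcomes of all participants who received that modality", usual-care participants included, with those who did not receive it.

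Other sections show how receipt and adherence come about:

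- Thermometry (Intervention description {11a}, part C): "The researchers may also decide it is no longer of value to continue the temperature measurements with a participant", and the example given is a participant in whom no hotspot is ever found. The background section on self-care says that a hotspot "can be a preliminary sign of inflammation preceding ulceration".
- Indoor footwear (part B): "participants are free to accept or decline the custom-made indoor footwear".
- Comparator {6b}: "Usual care may thus include one or more of the enhanced therapy interventions".

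The Strengths and limitations section concedes that the separate contributions of the modalities may not be identifiable. It then turns to these per-protocol analyses, through which "we aim to gain further insights into the effects of the individual treatment modalities".

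**The concern.** Randomisation protects only the comparison of enhanced therapy with usual care. Each comparison in {20b} re-sorts participants by something that happens afterwards. Two separate problems follow.

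The first is confounding by the rest of the bundle. In (iii), the recipients of any one modality come mainly from the enhanced arm, and the non-recipients mainly from usual care. The contrast for thermometry is therefore close to the contrast between the arms. The same holds in (ii) when adherers to one modality are set against all controls.

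The second is selection by risk. If thermometry is stopped because no hotspot appears, and hotspots can precede ulcers, those who stop are plausibly at lower risk. If footwear adherence is read partly from data after an ulcer, the outcome may influence the exposure.

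At stake is the reading of which modality works. The article offers no other analysis for that question.

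**Working it through.** **Inputs from the protocol article.** Ulcer risk is 37% in usual care and 15% in enhanced therapy (Sample size {14}). The sample is 126, or 63 per arm. The expected frequency in the enhanced arm is 0.75 for thermometry and 0.95 for indoor footwear (Table 1).

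**The plan's own figure.** For 37% against 15%, two-sided 5%, 80% power and 1:1 allocation, the pooled-variance formula gives 62 per group, against 61 stated. Power with 61 per group is 79.9%. The stated 122 is reproduced to within 2 participants and is not in dispute.

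**Check 1: bundle confounding in (iii).** Assume that the bundle achieves 15%, that thermometry adds nothing, that receipt is unrelated to risk, and that no control receives thermometry. Read the 0.75 as the share of the enhanced arm that receives it.

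- Recipients: 0.75 × 63 = 47.25 participants at 15.0%.
- Non-recipients: 63 controls at 37% and 15.75 enhanced-arm participants at 15%. Their risk is (63 × 0.37 + 15.75 × 0.15) / 78.75 = (23.31 + 2.36) / 78.75 = 32.6%.
- Apparent risk ratio for a useless modality: 15.0 / 32.6 = 0.46.

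The same step for indoor footwear at 0.95, supposing instead that it is the inert component, gives (23.31 + 3.15 × 0.15) / 66.15 = 36.0% in non-recipients against 15.0%. If everyone in the enhanced arm receives the modality, the contrast is simply 15% against 37%.

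In 10,000 simulated trials of the 0.75 case, comparison (iii) was significant in favour of thermometry in 61%, and adherent-versus-control in 75%. Comparing recipients with non-recipients inside the enhanced arm gave 15.0% against 15.0%, and was significant in 3.4% + 1.3% = 4.7% of trials.

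**Check 2: selection by risk in (i) and (ii).** The documents give no inputs for this, so all values below are assumptions. Thermometry has no effect, overall risk is 37%, and 40% of participants are high-risk. Participants who stop are counted as non-adherent.

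- Strong case: risks 55% and 25%; 95% of high-risk and 55% of low-risk participants continue. Continuers: (0.38 × 0.55 + 0.33 × 0.25) / 0.71 = 41.1%. Stoppers: (0.02 × 0.55 + 0.27 × 0.25) / 0.29 = 27.1%. The risk ratio is 1.52. Adherent-versus-non-adherent was falsely significant for harm in 16.4% of simulated trials, against a nominal 2.5%.
- Mild case: risks 45% and 31.7%; 90% and 65% continue. The result is 38.1% against 33.8%, a risk ratio of 1.13, with 4.2% falsely significant for harm.

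For apparent benefit, lower-risk people must adhere more, which the hotspot rule does not produce. With risks of 55% and 25% and adherence of 45% and 75%, the result is 33.6% against 42.8%, a risk ratio of 0.78, with 12.0% falsely significant for benefit. With risks of 45% and 31.7% and adherence of 55% and 68%, the risk ratio is 0.95, with 3.7%.

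**Benchmark.** In all these scenarios where the modality and the bundle both do nothing, the randomised comparison rejected in 5.2% to 5.6% of simulated trials. Sorting by use does not affect it.

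**The case against.** These are additional analyses. The article condenses a fuller protocol, and adherence definitions, covariates and exposure timing are commonly left to an analysis plan that is not shown. This stands in part: the lack of a stated adjustment is not itself a fault. But {20b} does fix who is compared with whom, including the pooling of arms, and that choice produces the result in Check 1.

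A reader might infer that the protocol makes its lowest-risk participants non-adherent. It does not say so. Stopping is discretionary, and part C describes it as part of personalisation, so counting it as adherent fits the text at least as well. Someone who measured for a time and was then stopped may also count as a recipient in (iii). The selection argument therefore belongs to (i) and (ii) and is conditional.

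A reader might also infer that the hotspot rule can bias in either direction. Alone it pushes only towards apparent harm. Nor does the text say that post-ulcer readings will classify adherence. It says only that adherence is calculated at 6 and 12 months and that wearing time is recorded throughout.

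Delayed receipt of indoor footwear might suggest bias from time already survived without an ulcer. Table 1 expects 0.95 uptake, leaving about 0.05 × 63 = 3 participants without it, so this route is minor.

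Finally, the Strengths and limitations section does not promise modality effects. It admits that they may not be identifiable and speaks of further insights. However, it offers these comparisons as the response to that limitation and mentions neither selection nor confounding by the other modalities.

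**Conclusion.** The point holds for modality-level conclusions only. The firmest part is comparison (iii): on the protocol's own 37%, 15% and 0.75, an inert thermometer shows about 15% ulcers against 33%. This needs no selection by risk. It does rest on reading the Table 1 costing frequency as the share who receive thermometry and on no receipt among controls. Receipt among controls would mix higher-risk participants into the recipient group and shrink the contrast.

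The adherence comparisons are open to selection and possible reverse causation. The size is not known: the assumed scenarios run from a risk ratio of 1.13 to 1.52 towards harm and from 0.95 to 0.78 towards benefit, so the bias may be small. The documents do not support a claim that large selection bias is certain, or that the trial's main results are compromised. The intention-to-treat comparisons in {20a} are untouched.

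**What to change.** - In (iii), compare recipients with non-recipients within randomised arm, or adjust for arm, instead of pooling crudely.
- In (i) and (ii), classify adherence only from data before the first ulcer.
- Count stopping or personalisation that the protocol permits as adherent.
- Adjust for the stratification factors (centre, time since healing) and baseline risk factors already collected, such as ulcer history, deformity and vascular status.
- Label all these results non-randomised and hypothesis-generating.
- In Strengths and limitations, state that the comparisons are confounded by selection and by the rest of the bundle.

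The cost is analysis-plan wording and modest programming, with no new data. The downside is imprecision. At 0.75 receipt, the enhanced arm has about 16 non-recipients and, at 15% risk, 15.75 × 0.15 = 2.4 expected ulcers among them. Adjustment can then support only a few covariates, and selection on unmeasured factors remains.
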